## Abstract

**Background:**

Perspectives of key stakeholders should be fully considered to enhance culturally appropriate strategies in end-of-life communication and strengthen healthcare service delivery. So far, little research evidence is available on Chinese patients’, families’, and healthcare professionals’ experiences with and perspectives of end-of-life communication in hospital settings.

**Aim:**

The current study aims to explore experiences, perceptions and suggestions of end-of-life communication among Chinese terminally ill patients, their families and healthcare providers.

**Methods:**

The phenomenology qualitative approach will be adopted. Semi-structured in-depth interviews and focus group discussions will be used to collect relevant data. Eligible terminally ill patients, family caregivers and healthcare providers will be recruited in two hospitals in Mainland China via purposive sampling. Thematic analysis will be performed to analyse data. The Standards for Reporting Qualitative Research (SRQR) checklist will be followed for reporting. This study has been registered at ClinicalTrials.gov (NCT05734781).

**Discussion:**

This qualitative study is, as far as we are aware, the first to specifically address patient/family-provider end-of-life communication in the Chinese social-cultural context. The results hold the potential to enrich current knowledge of end-of-life communication, navigate culturally appropriate communication strategies, and inform the development of related training programs for healthcare providers in hospital settings.

## Introduction

It has been found in a systematic review included 20 American studies that effective end-of-life communication is associated with quality end-of-life care, such as lower end-of-life care costs (median US$1,048 vs US$23,482; *P* < .001); less intensive care near end-of-life (ORs 0.26–0.68); and more hospice use (ORs 1.79–6.88) [1]. End-of-life communication refers to a series of highly individualised conversations regarding death and dying, such as disclosure of prognosis, advance care planning, and goals of care discussions [2–5]. It is an ongoing and iterative process and is also related to a patient’s transition to different settings [6].

Early end-of-life communication is widely advocated in the context of a serious illness, meaning such conversations should be started as soon as a patient has been identified as dying [1, 6–9]. Hospitals are common institutions where some patients are diagnosed with end-of-life conditions, seek any possible treatments and transfer to other healthcare settings [6, 10]. Given this, healthcare providers in hospital settings play an essential role in initiating and facilitating end-of-life communication [11, 12]. They are expected to accommodate patients’ preferences for information and shared decision-making while being sensitive to their emotional needs and vulnerabilities [13]. However, partly due to the curative culture and acquiescence of life-sustaining treatments, end-of-life communication has often been neglected or occurs very close to patients’ deaths in hospital settings [6, 9].

As the significance and benefits of end-of-life communication have been recognised in recent years, it is suggested to be integrated into routine clinical procedures for patients with serious illnesses [9]. Understanding the accounts of main stakeholders directly involved in end-of-life communication is a priority to organise meaningful communicative practice in a systematic approach and embed it in practice regularly [14]. Notably, existing research has primarily investigated from the vantage point of healthcare professionals, especially physicians [15–18]. There is a shortage of evidence about end-of-life communication from the views of other stakeholders, particularly patients with advanced diseases and relatives of such patients. Parker et al. [19] reviewed patients’ and their families’ information preferences regarding dying, life expectancy and future care. They discovered that the evidence is largely made up of studies conducted in specific populations from English-speaking and Northern European countries which may not be generalisable to people from different cultural backgrounds. O’Connor et al. [20] explored hospitalised patients’ experiences of goals of care discussion and decision-making process, which is only a part of end-of-life communication. Patient and family experiences and perspectives on the end-of-life communication process need further exploration and analysis to support the development of effective end-of-life communication system, enhance education and training for healthcare professionals in hospital settings, and foster the improvement of communication practice.

Our previous review of the international literature on end-of-life communication strategies emphasised the imbalance between the amount of evidence from Anglo-Saxon and non-Anglo-Saxon nations, which hinders a thorough comprehension and comparison of end-of-life communication in various sociocultural situations [21]. Moreover, recent research findings reinforce the influence of Chinese culture and philosophy on end-of-life communication. For instance, the traditional understandings and conceptualisations of death (e.g., discussion about dying and death is taboo and regarded as unlucky and harmful) impede the promotion of end-of-life communication; and the family-centred decision-making style may conflict with patient’s autonomy [15]. Previous studies explored the working experiences of Chinese physicians and nurses who work with advanced cancer patients [22, 23]; nurses’ attitudes towards death and dying [24] and end-of-life care [25]; family communication experiences [26]; patients’ understanding of death [27] and advance directive preferences [28]. Nevertheless, little is known about Chinese patients, families and healthcare providers’ experiences and perceptions of client-provider end-of-life communication. In addition, no empirical evidence on end-of-life communication strategies from a Chinese perspective has been found.

## Materials and methods

### Aims and objectives

This study aims to explore stakeholders’ (patients, families and healthcare providers) perspectives on end-of-life communication in Chinese hospital settings. More specific objectives are to (1) describe end-of-life communication experiences of Chinese terminally ill patients, families and healthcare providers, (2) understand their perceptions, attitudes and beliefs of end-of-life communication, (3) collect their suggestions and expectations on improving end-of-life communication, and (4) develop culturally appropriate communication strategies in the Chinese social-cultural context. The research questions are as follows: (1) what experiences do Chinese terminally ill patients, families and healthcare providers have in end-of-life communication in hospital settings? (2) what are their perceptions, attitudes and beliefs of end-of-life communication? (3) what are their suggestions and expectations for improving end-of-life communication? (4) what are the culturally appropriate communication strategies in the Chinese social-cultural context?

### Study design and setting

A phenomenology qualitative approach will be performed, which emphasizes deriving meaning from comprehensive descriptions of lived experiences related to a phenomenon [29]. We will adopt face-to-face interviews and focus group discussions to unearth participants’ experiences and perspectives. Semi-structured in-depth interviews with patients and family caregivers will be conducted respectively. In-depth interviews are helpful when the study is designed to understand and generate in-depth personal accounts [30]. Due to sensitive end-of-life-related topics in the interviews, these interviews will be conducted separately to encourage the engagement of participants. Focus group discussions will be arranged with healthcare providers, allowing them to discuss end-of-life communication and generate group interactions and creative thinking [30]. To avoid power differentials and professionally based hierarchies that may affect participation negatively [31], focus group discussions will be conducted with physicians, nurses and other healthcare professionals (such as anaesthetists and psychotherapists), respectively. For healthcare providers unwilling or unable to join the focus group discussions, semi-structured in-depth interviews will be conducted. Eligible patients, family caregivers and healthcare providers will be recruited in two hospitals in Hangzhou, China. The two hospitals are large public Grade-A tertiary hospitals (the highest level of hospitals in mainland China) and receive patients from all over the country. The departments involved will be oncology, radiotherapy, cardiology, hematology, nephrology, respiratory and critical care medicine.

### Participants

Purposive sampling methods will be adopted. The variation of participants’ characteristics (such as gender, age and education level of patients and families; disciplines of healthcare providers) will be considered as much as possible to ensure the breadth of relevant views [32]. Besides, both cancer and non-cancer patients will be included as they are both key informants with the knowledge or experience of our interest phenomenon [3, 33]. There is no gold standard on how large the sample size would be adequate in qualitative research. Thus, the sample size in this study will be decided following the principle of information saturation, which means the recruitment of participants will stop when the research topic has been thoroughly investigated [34]. Generally, consider 5 to 25 participants to provide sufficient data [35]. For a medium-sized research study, three to six focus groups are deemed adequate [30]. Around 20 patients and 20 family caregivers will be interviewed, and 3 to 6 focus groups, 4 to 8 participants each, will be arranged for reference in this study.

Included patients should: (1) Be aged older than 18 years. (2) Have a defined incurable life-limiting illness with a likely life expectancy of fewer than 12 months [36], according to the consultation with the patient’s physician. (3) Have been informed of disease diagnosis and treatment. (4) Be able to speak Mandarin and express clearly. (5) Be able to provide informed consent. Included family caregivers should: (1) Be aged older than 18 years. (2) One of the terminally ill patient’s primary family caregivers who are familiar with the patient’s situation, which is defined in this study as lived with or visiting patients at least twice a week in the past month. (3) Have been informed of the patient’s disease diagnosis and treatment. (4) Be able to speak Mandarin. (5) Be able to provide informed consent. Patients and family caregivers with severe auditory or cognitive impairment will be excluded. Included healthcare providers should: (1) Be nurses, physicians or other healthcare professionals. (2) Be experienced in providing treatment or care to patients with advanced, life-limiting illnesses (whose likely life expectancies of fewer than 12 months) and family caregivers of such patients for at least five years [37]. (3) Consent to participate in the study.

When approaching the eligible participants, firstly, the researcher will contact the relevant department head for consent and permission to enter the ward. Secondly, patients, family caregivers, and healthcare providers who meet the inclusion and exclusion criteria will be approached and recruited by the first author. Before approaching patients, the patient’s physician will be consulted on patient eligibility (patient’s medical record will be accessed by the physician and reviewed together by the first author, if necessary) and be sought approval on the patient’s possible participation in interviews. Additionally, a promotional poster detailing the nature and purpose of the research project will be posted on the Hospital’s notice board to attract possible participants who can self-select to partake in and contact researchers. Each eligible informant will be met in person to foster relationship development, build trust, enable inquiries and clarification requests.

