Tell me about any communication experiences that you have had with healthcare providers.	What topics were covered?How did you communicate…? • Diagnosis and prognosis *(e*.*g*., *health condition; clinical course; treatment uncertainties and limitations; and life expectancy)* • Advance care planning *(i*.*e*., *discussions of future care; may include the individual’s concerns*, *wishes*, *values*, *understandings*, *and preferences)* • Goals of care *(i*.*e*., *discussions of current care and decisions; may include specific medical interventions*, *such as whether to utilise life-sustaining treatments)* • Death and dying *(e*.*g*., *end-of-life wishes; care for psychological*, *spiritual*, *and existential problems; arrangements after patients’ death; and bereavement support)* Who was present?When and where did the communication occur?
How did you feel about the communication?	Is anything impressive or annoying during the communication process? Why?
What do you think of the communication?	Are they good? Why?
Perception, attitude and belief	
If your (the patient’s) condition continues getting worse, or the curative treatment effect is not satisfactory, do you think it is necessary for healthcare providers to have end-of-life communication with you?	Why or why not?
What is your understanding of end-of-life communication?	Is anything important for you to discuss with healthcare providers?
Strategy	
How would you like the healthcare provider to have end-of-life communication with you?	How to communicate…? • Diagnosis and prognosis • Advance care planning • Goals of care • Death and dying What specific words or phrases do you think healthcare providers should use? Would you like to give me an example? Who do you think should initiate end-of-life communication with you? Who should be involved? When and where are appropriate?
Suggestion	
If you are invited to give suggestions to healthcare providers who would like to have end-of-life communication with you, what would you say?	E.g., for healthcare providers who do not have much experience in end-of-life communication

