### Data management

All raw data will be stored securely on a password-protected computer. Paper copies of the consent form will be kept separately in a locked cabinet for five years, only accessible to the researcher team. Following the storage period, all personal information will be deleted.

Previous evidence [20, 26, 40] suggested that interviews were more helpful than detrimental and that there has not been any data to suggest that participants have suffered negative long-term consequences or have been referred for counselling due to being interviewed. Moreover, interviews may be therapeutic for participants by evoking hidden feelings and leading them to a new understanding of the events [44]. The interviews in this study will mainly include recalls of the experiences of end-of-life communication instead of real-life discussions regarding the diagnosis and prognosis of life-limiting illnesses. However, it is still likely to remind participants of past or current experiences that may elicit distress and discomfort, cause the risk of harm and precipitate emotional responses such as grief, anger, anxiety and fear. For example, patients and family caregivers may be reminded of poor prognosis or disease deterioration; emotional exhaustion or even conflict experiences in difficult communication among healthcare providers. We should consider that end-of-life communication is a sensitive topic in nature. Each people involved in sensitive research could be affected, including both participants and researchers, but avoiding it could be perceived as a failure to accept responsibility and a deprivation of participants’ agency [47]. Therefore, to minimise the risk of harm, safeguard vulnerable participants morally and ethically, and yield rich and meaningful data, some reasonable and appropriate safety measures will be taken. A risk assessment and distress protocol (Table 2) is prepared by the researchers, inspired by previous work on sensitive interviewing [44], to deal with distressed participants. Participants will be informed that they can refuse to answer questions or withdraw from the study at any time.

**Table 2 pone.0296342.t002:** A risk assessment and distress protocol.

Risks	Considerations	Measures
Risks to the participants		

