Some limitations should also be noted. First of all, it might be challenging to avoid a possible participation bias because participants who volunteer for the study are likely to be more interested in the topic and hold different opinions from those who are not interested in the topic. However, keeping the participation voluntary is essential to avoid coercion in participants’ recruitment. Also, we will include participants with as many different characteristics as possible to ensure that relevant perspectives are taken into account. Second, the included patients and family caregivers have been informed of disease diagnosis and prognosis, as we consider that it is sensitive and difficult to talk about end-of-life issues with Chinese patients and their families who have hope for a cure. This may lead us to ignore the views of end-stage patients who do not know their prognosis. Third, we used only semi-structured interviews and focus group discussions to recall participants’ past communication experiences and collecting relevant data. Such recollections and recollection-based descriptions may be inaccurate or incomplete. Other methods, such as direct participant observation, although it will be time-consuming to capture these end-of-life communications, may yield richer data.

The dissemination plan mainly includes sharing and applying research findings to practice. We will publish the results in international peer-reviewed scientific journals and present them at conferences. Key findings and practical implications will be communicated to the general public, practitioners and policymakers at domestic seminars.

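### The eligibility criteria require knowledge of diagnosis and treatment, but the limitations say participants know the prognosis, so the enrolled population may not be the one described

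*Protocol article*

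**What the plan says.** The Participants section of the protocol article lists five inclusion criteria for patients and five for family caregivers. Criterion 3 sets what each person must already have been told. For patients it is "Have been informed of disease diagnosis and treatment". For caregivers it is "Have been informed of the patient’s disease diagnosis and treatment".

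Terminal status is a separate condition, patient criterion 2: "Have a defined incurable life-limiting illness with a likely life expectancy of fewer than 12 months", established "according to the consultation with the patient’s physician".

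The limitations paragraph of the Discussion describes the same people differently. It says that "the included patients and family caregivers have been informed of disease diagnosis and prognosis", and explains that end-of-life matters are delicate and hard to raise with people who still hope to be cured. It then draws the consequence: "This may lead us to ignore the views of end-stage patients who do not know their prognosis".

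The guide for patients and families (Table 1, Data collection procedures) asks, if the condition worsens or curative treatment disappoints, "do you think it is necessary for healthcare providers to have end-of-life communication with you". The Data management section says that the interviews "will mainly include recalls of the experiences of end-of-life communication instead of real-life discussions" about diagnosis and prognosis.

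**The concern.** The limitations paragraph describes a deliberate restriction and its price. The criteria that decide who enters do not contain that restriction. Recruiting staff will apply the criteria, and readers of the results will rely on the limitations paragraph.

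Two things are at stake.

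- **Who was studied.** If prognosis-unaware people are enrolled, the article names as missing a group that is in fact present. Transferability would then be judged against the wrong population. The first objective is to describe experiences of end-of-life communication, and people who have not been told the prognosis may have had little of it.
- **What the interview may raise.** A participant who has not been told the prognosis could be asked about end-of-life communication concerning their own illness, or that of their relative.

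The article's own background makes unawareness plausible. The Introduction describes talk of death as taboo in Chinese culture, family-centred decisions that may conflict with patient autonomy, and end-of-life conversations in hospitals that are often neglected or held very late.

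**Working it through.** No sample-size or error-rate calculation is involved. The check compares the text of the sections and makes one count.

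**Step 1. The two descriptions.**

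| Place | What the patient or caregiver must know, or is said to know |
|---|---|
| Participants, patient criterion 3 | Diagnosis and treatment |
| Participants, caregiver criterion 3 | The patient's diagnosis and treatment |
| Discussion, limitations | Diagnosis and prognosis |

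These are different conditions. Knowing the diagnosis and the treatment does not imply having been told the prognosis.

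**Step 2. Does another criterion close the gap?** Take a patient who knows the diagnosis and treatment but has not been told the prognosis.

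- Criterion 1 (age): can be met.
- Criterion 2 (incurable illness, life expectancy under 12 months): can be met. It is settled with the physician and is a fact about the patient, not about what the patient knows.
- Criterion 3 (diagnosis and treatment): met.
- Criterion 4 (Mandarin, clear expression): can be met.
- Criterion 5 (able to consent): can be met.

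The only stated exclusion is severe auditory or cognitive impairment. The patient is eligible under the Participants section, yet the Discussion counts such patients as left out. The same reasoning applies to caregivers under their own five criteria.

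**Step 3. Does the recruitment procedure close the gap?** Before a patient is approached, the physician is consulted on eligibility and asked to approve participation. Eligibility here means the written criteria, which omit prognosis, and no awareness check is stated. The consultation is described for patients only. People who respond to the poster contact the researchers themselves, and no awareness check is stated for them either.

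**Step 4. What would such a person be asked?** Main questions in the patient and family guide:

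| Block | Main questions | Name end-of-life communication | Forward-looking among those |
|---|---|---|---|
| Experience | 3 | 0 | 0 |
| Perception, attitude and belief | 2 | 2 | 1 |
| Strategy | 1 | 1 | 1 |
| Suggestion | 1 | 1 | 1 |
| Total | 3 + 2 + 1 + 1 = 7 | 0 + 2 + 1 + 1 = 4 | 0 + 1 + 1 + 1 = 3 |

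The second perception question names the term but asks about present understanding, so it is not forward-looking. The three forward-looking questions all concern communication with the participant in person.

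**Step 5. How many people?** The plan gives about 20 patients and about 20 family caregivers as reference figures. It gives no rate of prognosis unawareness, so no count of affected interviews can be derived.

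**The case against.** The strongest reply is that this is a wording slip with little practical consequence, because several protections already exist. The physician must approve each patient's participation and may well hold back someone unsuited to the topic. The first question that names end-of-life communication is conditional and tells nobody that they are dying. Consent is required, the poster states the nature and purpose of the research, participants may refuse questions or withdraw, and Table 2 provides a distress protocol. All of this stands as mitigation. None of it is stated to test awareness of prognosis, and the distress protocol acts only after distress has arisen. Nor do these protections bring the criteria into line with the limitations paragraph.

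A reader might also infer more than the text supports.

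- **That the recall statement in Data management is wrong.** The life-expectancy and after-death prompts sit under the first experience question and ask which topics have already been covered. They are recall prompts and fit that statement. Asking for an opinion is also not the same as holding a prognosis discussion.
- **That the authors said they meant to avoid disclosure.** The stated reason is sensitivity and difficulty; disclosure is not mentioned.
- **That such patients do not know they are incurably ill.** Not having been told a prognosis is a narrower condition, and these patients do know their diagnosis and treatment.

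**Conclusion.** The inconsistency is real and stands in the current text. The criteria ask for knowledge of diagnosis and treatment, the limitations paragraph says diagnosis and prognosis, and nothing else in the article makes awareness of prognosis a condition of entry. The population enrolled may therefore differ from the one described, and an interview may raise prognosis with someone who has not been told it.

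The finding is that such people can be enrolled. A reader might infer that they will be, or attach a number to them. The documents do not support either: sampling is purposive, the physician approves each patient, and any rate of unawareness would be a guess.

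This should be fixed, but it does not undermine the design. The existing protections lower the risk to participants, and the correction is small. The conclusion rests only on reading the criteria as written; it assumes no unstated awareness check in practice.

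**What to change.** Reconcile the Participants section with the limitations paragraph so that both describe the same population. There are two routes.

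1. **If prognosis is intended**, as the limitations paragraph indicates, extend criterion 3 for patients and for caregivers to include having been informed of the prognosis. Confirm it in the physician consultation already planned, and apply the same check to caregivers and to people who respond to the poster.
2. **If treatment is intended**, keep the criteria and correct the limitations paragraph so that it no longer says that included people know the prognosis or that prognosis-unaware people were left out.

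Recruitment began on May 4, 2023, with data collection expected to finish in October 2023, so a change to the criterion comes after enrolment has started. Record the awareness status of those already enrolled, so that the report can describe the actual sample.

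The first route costs an amendment to the criterion, one more screening item and a slightly narrower recruitment pool. The second costs a change of text.

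### For patients the researcher approaches, the treating physician holds an open-ended approval over interviews that cover that physician's own communication, and the protocol does not acknowledge this gate

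*Protocol article*

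**What the plan says.** The protocol article, section Participants, gives the treating physician three functions in patient recruitment.

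- **Prognosis.** A life expectancy under 12 months is established "according to the consultation with the patient’s physician".
- **Eligibility.** "Before approaching patients, the patient’s physician will be consulted on patient eligibility", with joint review of the medical record where needed.
- **Approval.** In the same sentence, the physician is also to "be sought approval on the patient’s possible participation in interviews". This is separate from eligibility, and no criterion for giving or withholding approval is attached.

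A second route follows directly: a poster on the hospital notice board is meant "to attract possible participants who can self-select to partake in and contact researchers". The text does not say whether physician approval applies to patients who come forward this way. No physician approval is described for family caregivers.

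Table 1 (Data collection procedures) uses one guide for patients and families. It opens with "Tell me about any communication experiences that you have had with healthcare providers" and goes on to evaluation, with the prompt "Is anything impressive or annoying during the communication process" and a question on whether the communication was good.

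The Discussion concedes that "participants who volunteer for the study are likely to be more interested in the topic", that patients who do not know their prognosis are missed, and that recall may be faulty. It does not mention selection by physicians.

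**The concern.** The person who decides whether an eligible patient may be approached has an interest in what that patient might say. A physician who avoids talking about dying, or whose patient is unhappy with how it was done, can decline without giving a reason. Bad faith is not needed, since a protective refusal by a physician who finds the subject too sensitive has the same effect. Selection into the patient interviews can then depend on the thing being studied.

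At stake are the patient accounts for the first two objectives (experiences; perceptions, attitudes and beliefs). The Discussion says the results will feed a communication training programme and inform practice and policy. Accounts drawn mainly from patients whose physicians were at ease with the subject could hide the deficits that such training should address.

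**Working it through.** The protocol states no figure on this point, so there is nothing to reproduce. The check sets the relevant sections side by side.

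1. **Is approval distinct from eligibility?** Yes. Participants names both in one sentence. The criteria listed there are age, prognosis, being informed of diagnosis and treatment, ability to speak Mandarin and express oneself clearly, and capacity to consent, with severe auditory or cognitive impairment excluded. Approval comes on top of these and is tied to none of them.

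2. **Does it act before the patient can choose?** Yes. It precedes any approach, so on this route a patient who is withheld is never asked.

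3. **Is the approver among those being evaluated?** In part. Table 1 asks about healthcare providers in general, on diagnosis and prognosis, advance care planning, goals of care, and death and dying. The treating physician is an obvious subject of such answers, though not the only one.

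4. **Is there a plausible mechanism in the document itself?** Yes. The Introduction says that end-of-life communication in hospitals is often neglected or comes very late, and that talk of death is culturally taboo. Either gives a physician a reason to refuse an interview on the subject.

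5. **Does any stated measure counter it?** None acts at this gate. The characteristics named for purposive variation among patients and families are gender, age and education, not communication experience. Saturation is judged on those interviewed and cannot show what patients never approached would have said. Member checking, dual coding and reflexive notes (Quality and rigor) all act after recruitment.

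6. **Are there ways round the gate?** Two partial ones. The poster may bypass approval, but the prognosis criterion still depends on the physician. About 20 family caregivers answer the same guide with no physician approval described.

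7. **Can the size be calculated?** No. The document gives neither the share of patients with poor communication nor any refusal rate. An illustration on wholly assumed inputs shows the range. Let half of eligible patients have had poor or no communication, let physicians withhold a fraction *a* of these and 10% of the others, and let all patients come by the approached route and accept equally often. The share with poor experience among those approached is 0.5(1 − *a*) / [0.5(1 − *a*) + 0.5 × 0.9]:
   - *a* = 0.2: 0.40/0.85 = 47%, about 9 of 20 patients
   - *a* = 0.4: 0.30/0.75 = 40%, 8 of 20
   - *a* = 0.6: 0.20/0.65 = 31%, about 6 of 20

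   These figures only restate the assumptions, and they describe a prevalence that this study does not set out to estimate. On these inputs the critical voices are thinned, not silenced.

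**The case against.** The strongest reply has four parts.

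- **The gate protects patients.** They are dying and may be distressed, and a researcher arriving unannounced could disclose something they do not know. This stands: a clinical check before approach is legitimate. It justifies a reasoned objection, but does not require an approval without stated grounds.

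- **This is purposive, saturation-guided qualitative work.** It seeks breadth of accounts, not an unbiased proportion, so a survey standard of bias does not apply. This also stands, and for that reason the illustration above carries no weight as evidence. The remaining worry is the loss of particular kinds of account, which matters to breadth as well.

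- **Poor experiences can surface elsewhere**, through the poster and through family caregivers. This stands in part. It limits the harm to the study as a whole, but caregivers do not replace patients as a separate planned group of about 20.

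- **A condensed article need not describe a refusal log.** This stands. The absence of a log is not counted as an error here. The point rests on what the article does state: an approval rule without grounds, and a list of limitations that omits its consequence.

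A reader might infer more than the document supports: that every patient must be cleared by the physician, that the interview is an appraisal of that physician, or that the patient accounts will be too favourable. The approval sentence covers researcher-initiated contact only, the questions concern providers generally, and nothing shows that physicians would in fact refuse for these reasons.

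**Conclusion.** The point holds as a limited one. On the researcher-initiated route, an interested party holds an approval with no stated ground, and this can select patients on the phenomenon under study. The stated limitations do not cover it: volunteer interest is the patient's own choice, and the loss of prognosis-unaware patients is described there as a consequence of who is eligible, whereas this is discretionary refusal of eligible patients.

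The direction would be towards under-representing poor or absent communication in the patient interviews. The extent is partial and cannot be quantified from the document. The conclusion assumes that physicians have some discretion in practice and that refusals are not independent of how communication went. It does not make the study invalid.

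**What to change.** - Limit the physician's role to confirming the written eligibility criteria and, where there is an objection to approach, recording a specific medical or psychological reason.
- State whether poster volunteers need physician approval, and do not extend an open-ended approval to them, since that would widen the filter.
- Keep and report counts of patients withheld, by reason and department.
- Name gatekeeper selection among the limitations in the Discussion.

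The cost is a short form, a few protocol sentences and a little physician time to record a reason; the protective check stays. Recruitment began on 4 May 2023 with data collection expected to end in October 2023. If it is complete, the limitation can still be stated and any counts that can be recovered reported.
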